
## **Sensitive Research Information\***

Does this research involve collection of sensitive information about the subjects that should be excluded from the electronic medical record?

No

## **Subject Privacy**

Privacy refers to the person's desire to control access of others to themselves. Privacy concerns people, whereas confidentiality concerns data. Describe the strategies to protect privacy giving consideration to the following: The degree to which privacy can be expected in the proposed research and the safeguards that will be put into place to respect those boundaries. The methods used to identify and contact potential participants. The settings in which an individual will be interacting with an investigator. The privacy guidelines developed by relevant professions, professional associations and scholarly disciplines (e.g., psychiatry, genetic counseling, oral history, anthropology, psychology).

All potentially eligible employees within the CVS-covered group will be contacted via existing communication channels through CVS. Potentially eligible employees will have evidence of diabetes medication use and/or CVD medication use in the CVS pharmacy database. These individuals will be sent letters (paper or email) describing the study and inviting them to enroll. Potentially eligible patients recruited from Penns Health system/LGH will be contacted by the study team via letter, email and phone calls. Interested employees will meet by phone with a study coordinator based at UPENN and be asked to provide informed consent. These individuals will have the option of entering data related to eligibility and their demographic and clinical characteristics through the Way to Health internet portal or by phone. Each potential participant will visit a local participating laboratory (through the Quest national chain of commercial laboratories or their doctor if they are from Penn Medicine/LGH) to

confirm that their LDL is 100 mg/dl. The Quest corporation has 24 hour appointment scheduling and 2,000 lab locations; these locations are in every state as well as Puerto Rico. The enrollment interview and baseline labs will allow investigators to determine final eligibility for the study.

#### **Data Disclosure**

Will the data be disclosed to anyone who is not listed under Personnel?

Vitality, Inc., MedSignals, Adheretech, Wisepill, the companies which records the responses from the electronic pill containers. Daily adherence information will be stored on their secure computers. Quest Diagnostics, the company that will be used for blood sample collection and analysis. Lab results from Quest will be made available via a csv file that Way To Health (WTH) can download directly from secure Quest servers. The Office of Human Research Protections at the University of Pennsylvania Federal and state agencies (for example, the Department of Health and Human Services, the National Institutes of Health, and /or the Office for Human Research Protections), or other domestic or foreign government bodies if required by law and/or necessary for oversight purposes A data and safety monitoring board organized to oversee this research

#### **Data Protection\***

- x **Name**
- x **Street address, city, county, precinct, zip code, and equivalent geocodes**
- x **All elements of dates (except year) for dates directly related to an individual and all ages over 89**
- x **Telephone and fax number**
- x **Electronic mail addresses**
- x **Social security numbers**
- x **Medical record numbers**
- x **Health plan ID numbers**
- Account numbers**
- Certificate/license numbers**
- Vehicle identifiers and serial numbers, including license plate numbers**
- Device identifiers/serial numbers**
- Web addresses (URLs)**
- Internet IP addresses**
- Biometric identifiers, incl. finger and voice prints**
- Full face photographic images and any comparable images**
- Any other unique identifying number, characteristic, or code**
- None**

Does your research request both a waiver of HIPAA authorization for collection of patient information and involve providing Protected Health Information ("PHI") that is classified as a "limited data set" (city/town/state/zip code, dates except year, ages less than 90 or aggregate report for over 90) to a recipient outside of the University of Pennsylvania covered entity?

No

#### **Tissue Specimens Obtained as Part of Research\***

Are Tissue Specimens being obtained for research?

No

#### **Tissue Specimens - Collected during regular care\***

Will tissue specimens be collected during regulator clinical care (for treatment or diagnosis)?

No

**Tissue Specimens - otherwise discarded\***

Would specimens otherwise be discarded?

No

**Tissue Specimens - publicly available\***

Will tissue specimens be publicly available?

No

**Tissue Specimens - Collected as part of research protocol\***

Will tissue specimens be collected as part of the research protocol?

No

**Tissue Specimens - Banking of blood, tissue etc. for future use\***

Does research involve banking of blood, tissue, etc. for future use?

No

**Genetic testing**

If genetic testing is involved, describe the nature of the tests, including if the testing is predictive or exploratory in nature. If predictive, please describe plan for disclosing results to subjects and provision of genetic counseling. Describe how subject confidentiality will be protected Note: If no genetic testing is to be obtained, write: "Not applicable."

N/A

## Consent

### *1. Consent Process*

**Overview**

All potentially eligible employees within the CVS-covered group will be contacted via existing communication channels through CVS. Potentially eligible employees will have evidence of diabetes medication use and/or CVD medication use in the CVS pharmacy database. These individuals will be sent letters (paper or email) describing the study and inviting them to enroll. Interested employees will meet by phone with a study coordinator based at UPENN and be asked to provide informed consent. These individuals will have the option of entering data related to eligibility and their demographic and clinical characteristics through the Way to Health internet portal or by phone.

**Children and Adolescents**

There will be no children or adolescents enrolled in this study.

**Adult Subjects Not Competent to Give Consent**

Adult subjects will be competent to give informed consent.

### *2. Waiver of Consent*

**Waiver or Alteration of Informed Consent\***

Waiver of written documentation of informed consent: the research presents no more than minimal risk of harm to subjects and involves no procedures for which written consent is normally required outside of the research context

**Minimal Risk\*****Impact on Subject Rights and Welfare\*****Waiver Essential to Research\*****Additional Information to Subjects**

**Written Statement of Research\***

Yes

**If no written statement will be provided, please provide justification**

**The following documents are currently attached to this item:**

*There are no documents attached for this item.*

## **Risk / Benefit**

### **Potential Study Risks**

Risks Involved in the Main Study. There are minimal risks associated with providing sweepstakes-based financial incentives to improve adherence to statins among individuals already prescribed this medication by their physicians. The main risk is loss of confidentiality, which will be protected as described below. Another small risk exists for local trauma (hematoma) during blood draw for cholesterol level /lipid testing. However, this is a minimal risk since blood will be drawn by skilled phlebotomists through Quest Diagnostics. There are no potential risks associated with any other measures or data to be collected. During the consent process, we will inform subjects of the risks associated with blood draws and loss of confidentiality. The following measures will be taken to minimize risks in this trial. First, enrollment criteria will limit participation to individuals who a) have been prescribed a statin prior to enrollment (confirmed through pharmacy records), b) deny a history of active liver disease, and c) deny allergies or adverse events to statins (including myopathy).. Third, participants will be informed about risks of liver and muscle inflammation with use of statins during the informed consent process. Fourth, during the trial, we will communicate with participants at 3-month intervals through Way to health and ask specifically about symptoms of muscle inflammation or new diagnoses of muscle or liver disease. Participants will also have the option of spontaneously reporting possible drug-associated complaints at any time. For the revised application, we have also reduced the expected value of the financial incentive from \$2.80 to \$1.40/day, which should reduce the possibility of undue incentive to continue the medication were side effects to develop. Lastly, we will alert prescribing physicians when any participant develops evidence of a clinically significant statin side-effect. In summary, given the low incidence of serious adverse effects with statins, our screening measures, the fact that participants have already been prescribed a statin, and the reduction in the magnitude of incentives, this intervention should confer substantial potential benefit but little incremental risk. No results will be reported in a personally identifiable manner. Electronic Data Security. The same procedure used for the analysis of automated data sources to ensure protection of patient information will be used for the survey data, in that patient identifiers will be used only for linkage purposes or to contact patients. The study identification number, and not other identifying information, will be used on all data collection instruments. All study staff will be reminded to appreciate the confidential nature of the data collected and contained in these databases.

### **Potential Study Benefits**

Participants in this study may not receive any direct benefits. Some may benefit directly by improving their adherence to statin medications and thus lowering their risk for future heart attacks, strokes and death, improved quality of life, and reduced medical care costs. The control group is unlikely to directly benefit, but this group will continue to receive usual care. Knowledge gained from the study will assist in development of interventions in others who are not adherent to their prescribed medications. The potential public health impact of a successful intervention to improve adherence to statin medications is enormous and could reduce the number of deaths from heart attacks and strokes by tens of thousands in the United States each year. The risks of loss of confidentiality are minimal in this study. Thus, the benefits of this research to the participants studied, and to society at large, far surpass the risks.

### **Alternatives to Participation (optional)**

To not participate in the study.

### **Data and Safety Monitoring**

The data and safety monitoring plan will have three parts. First, the BMIC will develop and implement methods of verifying entered data and of quality control. Second, the PI will be directly responsible for

identifying and reporting all serious adverse events, protocol deviations/violations and unanticipated events to the IRBs and funding agency promptly, as appropriate. The PI will also report all adverse events, accrual rates, retention rates, and all other logistical issues to the DSMB (described below) at least biannually (and more frequently if there are serious adverse events). Third, there will be a DSMB responsible for monitoring the trial. A written research protocol will undergo formal institutional scientific and institutional review board (IRB) review at the University of Pennsylvania (UPENN) to ensure protection of the rights and welfare of human research subjects. Specifically, the multiple principal investigators (PIs) and the IRB will be responsible for ensuring risks to human subjects are minimized, risks are reasonable, subject selection is equitable, the research team has access to adequate resources to conduct the study, the informed consent process meets regulatory and ethical requirements, adequate provision is made to protect human subjects by monitoring the data collected and there are adequate provisions to protect subject privacy per HIPAA regulations and confidentiality of data. All senior/key personnel and research staff who will be involved in the design and conduct of the study must receive education in human research subject protection from a training program that is approved by a properly constituted independent Ethics Committee or Institutional Review Board. The multiple PIs will be responsible for ensuring that project faculty and staff have the equipment and training required to protect privacy and confidentiality and will monitor and document that these individuals are properly certified. If new senior/key personnel and staff become involved in the research, documentation that they have received the required education will be included in the annual progress reports. The UPENN Office of Regulatory Affairs currently requires HIPAA training upon designation as research investigator/staff and recertification in human research subject protection every three years. The UPENN IRB will serve as the IRB of record for any external ethics review boards or IRBs applicable to researchers from other institutions who may have access to human research subjects identified data. Data and Safety Monitoring Board. The DSMB will be composed of experts in clinical trials, medical economics, general internal medicine, and biostatistics, along with multiple PIs Drs. [name] and [name] as non-voting members. We consider the proposed trial to be relatively low risk. Therefore, we have arranged for a monitoring committee that is assigned to review the study and staff training protocols, monitor the trial for safety and adverse events, and conduct a semi-annual meeting. These members will not be involved directly with the trial. The members that we propose to serve on this committee and their activities are: 1) [name], who is Assistant Professor of Medicine at Harvard Medical School, a cardiologist and member of the Thrombolysis in Myocardial Infarction (TIMI) clinical trials group. He has led multiple RCTs related to cardiovascular disease (CVD), including as PI of the multi-center, international PRINCIPLE-TIMI 44 trial that compared the effects of high-dose clopidogrel with prasugrel on platelet function and inflammation. He was also lead author of the PROVE IT-TIMI 22 substudy, which focused on the safety on the safety and efficacy of achieving very low LDL with intensive statin use; 2) [name], who is Associate Professor of Biostatistics at Columbia University Mailman School of Public Health. [name] has extensive experience in the conduct, analysis and interpretation of clinical trials. Among other responsibilities, she serves as the co-principal investigator of the NIH funded TBI Clinical Trial Network. 3) [name], who is Associate Professor of Medicine at Harvard Medical School. His health policy research focuses on adherence to evidence-based treatments for CVD; he was the PI of the recently-completed MI FREEE trial that randomized post-myocardial infarction patients to reduced copayments for secondary prevention medications. Risk of loss of confidentiality will be minimized by making the Way to Health Portal, which contains the study consent and survey data, accessible only to trained study staff. Each subject will be assigned a unique identifier without identifying information, and any data that is exported from the portal for analysis purposes will be entered into an electronic database using only the unique identifier. Only trained study staff will have access to the code that links the unique identifier to the subjects identity. Electronic data will be stored on secure, password-protected firewalled servers at UPENN. The DSMB members will perform several duties. First, they will review and approve the research protocol and plans for data and safety monitoring prior to initiation of the study. Second, they will evaluate the progress of the trial. This will include assessment of data quality, participant recruitment, accrual and retention, participant risk versus benefit, performance of trial sites, and study outcomes. This assessment will be performed at meetings every 6 months during the clinical trials and more frequently if needed. Third, they will make recommendations to ensure that all of the issues above are appropriately addressed. The multiple PIs of the project will be responsible for responding to all recommendations of the DSMB and submitting DSMB reports to the respective IRBs.

**The following documents are currently attached to this item:**

*There are no documents attached for this item.*

**Risk / Benefit Assessment**

Poor statin medication adherence is a major public health problem with few scalable, cost-effective solutions. This study is designed to test two novel interventions that, if successful, will provide the research and public health communities with critically important information about these new methods. This approach has potentially broad generalizability in treating people at risk for coronary events and death nationally, as these types of incentives could be set up by insurers and broadly utilized. Moreover, the interventions can serve as a model for improving adherence among other medications for chronic diseases. Because of the large scientific and public health benefits of the knowledge gained from this study, the minimal risks to participants are reasonable in relation to the importance of the knowledge that reasonably may be expected to result.

**General Attachments**

*The following documents are currently attached to this item:*

Cover Letter (irbcoverletter\_6.20.2019.doc)

## 1 Descriptive Analyses

1. Baseline characteristics. (Table 1) Describe the two populations (Penn Medicine & Lancaster General) and the sample, stratified by arm (include numbers (%) missing for each variable)
  - a. Age
  - b. Sex
  - c. Race/ethnicity
  - d. Income/household size/financial situation/marital status
  - e. Education
  - f. Health condition
  - g. Patient Activation Measure (PAM)
2. LDL-c Descriptive statistics
  - a. Baseline LDL-c (mean, median, IQR, SD, 95% CI on mean)
  - b. Repeat for LDL-c and change from baseline,  $\Delta_{LDL}$ , at 3,6,9 months and 12 & 18 months in cross-sectional fashion
  - c. Determine rate of missing LDL-c by arm at 3,6,9 months and 12 & 18 months

## 2 Inference

### 2.1 Primary outcome

- Linear regression model of primary outcome,  $\Delta_{LDL}$ , for month 12 of the study as a function of study arm with baseline LDL-c and population included in the model (Penn Medicine & Lancaster General)
- Primary analysis uses multiple imputation (MI) to adjust for missing data
  - Describe subjects who are missing 12-month LDL-c data (within 60-day window)
  - Imputation model: includes arm assignment, and all of the baseline covariates described above.

- Hypothesis testing as described in the protocol and in previous Habit Formation Trial. Use a family-wise type I error rate of 0.05.
  - Compare each arm to control using Holm-Bonferroni correction
  - Compare any arms that are significant (adjusted  $p < .05$ ) to each other using Tukey's Honest Significant Difference.

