
suggests that a reduction in 10 mg/dl in LDL potentially reduces CVD events by 5%. We present results from a two-step approach to the power calculation intended to detect differences of 10 mg/dl or greater between the control and each intervention arm, as well as a 5 to 10 mg/dl difference between the most and least effective intervention arms. Thus Step 1 compares each of the intervention arms versus control (3 comparisons); Step 2 compares each of the intervention arms to each other arm (3 additional comparisons). For these sample size estimates, we assumed a standard deviation of 28 mg/dl (based on a prior RCT). The nominal experiment-wise two-sided Type 1 error rate of 0.05 was maintained in step 1, by using a Bonferroni correction (i.e.,  $\alpha=0.017$ , derived as  $0.05/3$  for 3 comparisons) and in Step 2 by using Tukeys honest significant difference. Many possibilities exist for differences between the three interventions and control; the table below considers three possibilities for a sample size of 160 per group. For differences of 10 mg/dl or larger between intervention and control, simulation studies indicate at least 80% power to detect differences between all 3 interventions and control. For differences of at least 10 mg/dl between interventions, we have at least 90% power to detect at least one difference among arms; for differences of 5 mg/dl or larger we have 82% power to detect at least one difference among arms. To ensure our sample size of 160 for the 12 month endpoint, we assumed a dropout rate of 14.5 % and inflated the sample size to 187 in each arm ( $n=748$  in the entire study) . Sensitivity Analyses: Between November 2015 and July 2016 the device failed at rates that exceeded rates obtained in our earlier studies. We anticipated that this might increase the variance of the primary outcome, with some subjects perhaps responding positively with increased compliance to statin medication and some negatively with decreased compliance. Positive responses might reflect increased intervention from study staff, or the swapping out of one device for another spurring increased compliance. Negative responses might reflect frustration, particularly on the Process arm or the Process & Outcome arm, with the inconsistent devices. We note that our completion rates for lab visits are close to our expected rates of 85%, suggesting that the device issue has not had an impact on subject retention. APPROACH 1: As a sensitivity analysis, we increased our assumed variance by 7% (SD 29 versus SD of 28) and we decreased our effect size in the Process alone and the Process & Outcome arms by 10%. Given that only XX subjects were affected for over a month, we believe this to be a very conservative calculation of the negative impact of the device issue. Table 2 above shows that, while our power has declined somewhat, we still have close to 80% power or APPROACH 2: As a sensitivity analysis, we increased our assumed variance by 15% (SD 30 versus SD of 28). Given that only XX subjects were affected for over a month, we believe this to be a reasonable assumption. Our study was designed to detect differences of 10 mg/dl between control and treated group as this difference is deemed clinically relevant. Table 3 below shows there is some decline in power, but overall we retain good power to complete the study successfully under a number of scenarios.

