### **Analysis Plan**

Data analysis plans. We will explore and describe participant attributes across the 4 arms using graphical approaches and summary statistics (means, medians, standard deviations and the interquartile range). The primary analysis will be intent-to-treat using a linear regression analysis of the effect of treatment assignment on the outcome of change in LDL from baseline to 12 months. The model will be stratified by center and baseline will also be added as a covariate in order to improve efficiency of the analysis. Secondary analyses will adjust for measures of socioeconomic status (SES) and educational attainment (EA). We will explore whether SES and EA act as effect modifiers. We will assess model fit using standard linear regression diagnostics. In additional exploratory analyses, longitudinal models will examine the series of LDL values over time, to determine the shape of the trajectory and consider whether those trajectories differ by treatment group. All hypothesis tests will be two-sided. As a secondary analysis, we will compare the effect of the interventions vs. control among the subgroup of patients who are African-American and/or Hispanic. To maximize the power for this exploratory analysis, we will pool participants in all three incentive arms and compare to control participants. Missing data: Given low rates of drop-out in our other financial incentive studies and because this trial is low-risk, we anticipate low rates of drop-out. As with our other studies, we are diligent in proactively encouraging complete follow-up. Generous participation incentives, as well as multiple reminders

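### SAP 2.1 tests process against outcome incentives only if both arms first reach significance against control; the protocol's Step 2 and its stated power carry no such condition

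*Combined protocol and SAP*

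**What the plan says.** SAP 2.1 sets out the confirmatory testing of 12-month LDL change in one bullet with two sub-steps. The overall instruction is "Use a family-wise type I error rate of 0.05". The first sub-step is "Compare each arm to control using Holm-Bonferroni correction". The second is "Compare any arms that are significant" (adjusted p below .05) "to each other using Tukey's Honest Significant Difference". The SAP does not say whether the Tukey family is the arms that passed, all three intervention arms, or all four arms. The bullet opens with "Hypothesis testing as described in the protocol and in previous Habit Formation Trial".

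The protocol's testing scheme is in the power and sample size text of the Accrual section. Step 1 compares each intervention with control: "The nominal experiment-wise two-sided Type 1 error rate of 0.05 was maintained in step 1, by using a Bonferroni correction". For the head-to-head comparisons it says "Step 2 compares each of the intervention arms to each other arm (3 additional comparisons", with Tukey's method and no condition on Step 1. Power for Step 2 is given as 82% for differences of 5 mg/dl or larger and at least 90% for differences of at least 10 mg/dl between interventions, at 160 per arm and SD 28 mg/dl. The protocol's Analysis Plan adds "All hypothesis tests will be two-sided" and no other multiplicity rule.

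**The concern.** The protocol's title, background and design section all present process versus outcome incentives as the question. Under SAP 2.1 that contrast is tested only when both arms are significant against control. If one incentive works and the other does not, the two are not tested against each other, and a reader is left to infer a difference from one significant and one non-significant result, which is not a test of that difference.

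Nothing else in the SAP fills the gap. Section 2.2 either repeats the primary analysis (complete cases, other adjustments, 18 months), and so carries the condition with it, or tests arms against control across visits. The between-arm estimates in Section 3 are exploratory and concern device failure.

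There is a second, smaller matter. The SAP states one family-wise rate of 0.05 but applies Holm at 0.05 and then Tukey at 0.05.

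**Working it through.** **Inputs.** From the protocol's Accrual section: 160 evaluable per arm, SD 28 mg/dl, four arms, 10 mg/dl against control, 5 to 10 mg/dl between interventions, two-sided 0.05. Assumed: normal outcomes, and effects written as process/outcome/combined in mg/dl against control. The condition is simulated as SAP 2.1 states it, with at least 300,000 trials per scenario.

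**Basic quantities.**
- Standard error of a difference: 28 × √(2/160) = 3.130.
- Degrees of freedom: 4 × 159 = 636.
- Tukey critical |t| = q/√2: 1.964 for two arms, 2.349 for three, 2.576 for four. The matching per-pair error rates are 0.0500, 0.0191 and 0.0102.

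**Step 1 of the check: the protocol's own Step 2 power.** This is the probability of at least one significant difference among the three intervention arms.

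| Assumed effects | Protocol states | Unconditional 3-arm Tukey | With SAP condition, Tukey on selected arms | With SAP condition, 3-arm critical value |
|---|---|---|---|---|
| 10/15/20 | 82% | 82% | 75% | 74% |
| 10/10/20 | at least 90% | 91% | 82% to 83% | 81% |

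The stated figures are reproduced without the condition and not with it.

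**Step 2: process versus outcome when the two differ by 10 mg/dl.** Without the condition, power depends only on that difference: 10/3.130 = 3.194, and Φ(3.194 − 2.349) = Φ(0.845) ≈ 0.80.

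| Effects | Contrast tested under SAP | Significant under SAP | Significant unconditionally |
|---|---|---|---|
| 10/0/10 | 3.3% | 1.7% | 80% |
| 10/0/0 | 1.8% | 1.1% | 80% |
| 15/5/15 | 36% | 23% | 80% |

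The first two rows have a simple explanation. If outcome truly equals control, the contrast is reached only when the outcome arm is falsely declared different from control. Holm limits that to 5%, so power for the contrast cannot exceed 5% at any sample size or process effect.

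**Step 3: error over both steps together.** The unfavourable pattern for the conditional plan is two equally effective arms and one null arm. When the effective arms always pass, Holm tests the null arm at the full 0.05 and Tukey adds its own per-pair error a on the two equal arms. The limit is 1 − 0.95 × (1 − a):
- two-arm Tukey: 1 − 0.95 × 0.95 = 0.0975;
- 3-arm value: 1 − 0.95 × 0.9809 = 0.068;
- 4-arm value: 1 − 0.95 × 0.9898 = 0.060.

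Simulated values:

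| Truth | SAP condition, two-arm Tukey | SAP condition, 3-arm value | No condition, Holm plus 3-arm Tukey |
|---|---|---|---|
| Nothing works | 4.4% to 4.5% | 4.4% to 4.5% | 8.3% |
| One null, two equal at 10 mg/dl | 5.7% to 5.8% | 4.4% to 4.5% | 5.7% |
| One null, two equal at 20 mg/dl | 9.7% to 9.8% | 6.8% | 6.8% |

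With three equally effective arms the conditional plan stays at about 5% or below (2.4% at 10 mg/dl, 5.0% at 20 mg/dl).

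**The case against.** Testing arms against control first and comparing only those that work is a recognised gatekeeping strategy, and it fits Specific Aims 1 to 3, each of which asks whether one incentive lowers LDL. That is true of the aims. It does not explain why the SAP invokes a protocol scheme with no condition, or why the sample size text quotes head-to-head power that the condition does not deliver.

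The protocol's scheme sits in a power section and is described as having two steps, so a conditional Step 2 might have been intended. The wording states no condition, though, and the figures match the unconditional test. The SAP also defers to an earlier trial that is not available here and may define the condition or the Tukey family. The conflict between the two texts remains until that is written down.

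The effect patterns behind the power table are not visible. 10/15/20 and 10/10/20 are assumptions that fit the stated powers, so the match is strong evidence but not proof. The loss of any-difference power in those patterns is moderate, roughly 7 to 10 percentage points; the severe loss is specific to one incentive working and the other not, or working only weakly.

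A reader might infer from the two separate 0.05 allocations that the plan's true error rate is close to 10%. The documents do not support that as a general statement. It needs two exactly equal arms at 20 mg/dl, twice the design effect, an exactly null third arm, and a two-arm Tukey test that the SAP does not specify. The protocol can also be read as holding 0.05 within each step, and on that reading each step holds its rate.

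**Conclusion.** The concern holds for the condition. SAP 2.1 and protocol Step 2 contradict each other, and the SAP's version can leave the title comparison without a confirmatory test. At the design assumptions (160 per arm, SD 28), a true 10 mg/dl advantage of process over an ineffective outcome incentive is declared significant in about 2% of trials under the SAP and 80% under the protocol's Step 2. The stated Step 2 powers belong to the unconditional test, given the assumed patterns.

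The error-rate point is secondary. A single overall 0.05 is not held in every configuration, but at 10 mg/dl the excess is under one percentage point and only with a two-arm Tukey, and there is no excess when nothing works. It calls for the scope of the 0.05 and the Tukey family to be stated. It does not show a seriously inflated trial.

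**What to change.** In SAP 2.1, delete the requirement that arms be significant against control before they are compared. Test and estimate all three intervention pairs from the primary model with 3-arm Tukey and adjusted 95% confidence intervals, listing process versus outcome first, whatever Step 1 shows. Replace the single family-wise statement with one saying that 0.05 is held within Step 1 (Holm) and within Step 2 (Tukey), and not across both. Where the SAP repeats the primary analysis, including at 18 months, the same rule should apply.

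This is a change of wording and needs no extra participants. The cost is that the probability of any false positive over both steps, if no incentive works, is 8.3% instead of about 4.4%, and the report should say so. If results have already been seen, the change should be dated and disclosed as a return to the protocol's Step 2.

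If one overall 0.05 is preferred, an all-pairs procedure is an optional trade-off. Tukey over all six pairs holds 5% with 73% power for any 10 mg/dl difference, including arm versus control; 80% would need about 183 evaluable per arm. Shaffer's step-down test gives about 78% for process versus outcome at 10/0/10, and lowers arm-versus-control power from 82% to 78% there and from 85% to 77% if all three arms work equally at 10 mg/dl.
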